### Secondary Outcomes

For validity evaluation, the secondary outcome includes incidence of delirium (subjects with delirium/total number of subjects × 100%) by 12 and 24 h after entering ICU. Time to weaning and extubation are recorded. Difficulty of nursing is evaluated by TISS-28 scoring system. RASS, BIS and PI are recorded every 30 min during medications. For safety evaluation, the secondary outcome includes 28-days survival, vital signs during medications, total dose and dose per kilogram body weight of analgesic and sedatives and incidence of rescue therapy in experimental group, side-effect report from usage of medications to 28 days after patients depart from intensive care unit. Side-effect is defined as hypotension, bradycardia, elevation of bilirubin, abnormal urine (Elevated urinary leucocyte/ketone body/bilirubin) in this study.

## Sample Size Planning

In this study, propofol was used as a positive control. The hypothesis is compared with propofol, Remimazolam Besylate for Injection has non-inferiority satisfied rate of sedation on ERAS patients under mechanical ventilation in ICU. Setting inspection level: α = 0.05, 1–β = 80%, the non-inferiority threshold is 10%. Subjects in experimental group and control group is 1:1. According to the results of previous clinical trials, the target sedation rate of the propofol group is 82% (11), assuming that the target sedation rate of the Remimazolam Besylate group is 92%, a total of 70 subjects (35 for experimental group and 35 for control group each) should be enrolled to meet inspection level. Sample size calculations allow for 15% loss of cases, a total of 84 subjects (42 for experimental group and 42 for control group each) are enrolled in this clinical trial.

## Recruitment

All participants will be recruited in hospital settings between the time of admitted and the time of surgery. Patients who both meet criteria of enhanced recovery after surgery (ERAS) and may potentially admitted to ICU are considered as potentially eligible patients. A member of the research team will approach the patient and/or their legally authorized representative (based on the law of the People's Republic of China) before the surgery. A brief screening evaluation will be conducted. If the patients fit all eligibility criteria, the purpose, gain and risks of this clinical trial will be detailed delivered to the patients and/or their legally authorized representative. A written informed consent is required to be finished if patient AND their legally authorized representative agree to join in this clinical trial. For patients who are too sick or who are not competent to give their own permission to enter the study, consent will be obtained from the patient's legally authorized representative (based on the law of the People's Republic of China).

## Allocation

Randomization will be carried out on the day of surgery immediately after the patients entered ICU and will be performed centrally through an online electronic data management system after confirmation with researchers that the patient is suitable for randomization. Participants will be randomly assigned to one of the two groups in a 1:1 ratio. Participants and their clients, researchers who are responsible for assessment, data recording and statistical analysis will be blinded to treatment assignment. The researchers will not be blinded to treatment assignment.

## Data Management

Data will be collected using an online data collection form via a secure, password-protected platform with predefined data fields. Based on the PUMC Intensive Care Medical Information System and Database (PICMISD), all bedside instruments, including monitors, mechanical ventilators, and blood gas analyzers are connected into a central server to achieve real-time data acquisition and synchronization. The clinical data of the patients involved in this study included (1) monitors parameters: respiratory rate (RR), heart rate (HR), mean arterial pressure (MAP), body temperature, central venous pressure (CVP), perfusion index (PI), bispectral index (BIS). (2) Data of arterial blood gas analysis (ABG), including lactate level, pO2, GAP, ScvO_2_. (3) Data of Biochemical laboratory analysis and evaluation scale. (4) Medication: usage and drip speed of vasoactive agent, liquid usage and balance, usage and drip speed of sedatives and analgesics. All data used in the statistical analyses were collected during the clinical trial. All identifiable data collected, processed and stored for the purposes of the project will be kept confidential at all times and comply with Good Clinical Practice guidelines for Research and the General Data Protection Regulation. The research project will be monitored closely by a certified external auditor to ensure that study activities are carried out in accordance with the protocol, good clinical practice and applicable regulatory requirements. Data quality will also be audited.

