### Eligibility Criteria

#### Inclusion Criteria

Meet criteria of enhanced recovery after surgery (ERAS);Mechanical ventilated when enrolled and have estimation of more than 10 h of mechanical ventilation in ICU;Aged between 18–75 years old and 18 ≤ BMI ≤ 30 kg/m^2^;Clearly know the purpose and objective of this clinical study and voluntarily enrolled.

Criteria of ERAS: (1) without dysfunction of nervous system or Glasgow Coma Score >12; (2) a satisfied glucose level (random blood glucose <11.1 mmol/L during screening stage) for diabetes mellitus patients; (3) Without acute coronary syndrome in recent 6 months; (4) Without bradycardia and third-degree atrioventricular block (except for patients with pacemaker) during screening stage; (5) systolic blood pressure >90 mmHg with no usage of vasoactive agent during screening stage; (6) without mental illness (schizophrenia, depressive disorder), cognitive dysfunction (identified by MMSE), epilepsy, history of abuse of psychotropic, or anesthesia medication; (7) without disorder of coagulation function (PT/INR/APTT > 1.5 × upper limit), bleeding tendency (active peptic ulcer), under treatment of thrombolysis and anticoagulant; (8) without disorder of liver function (ALT/AST > 2 × upper limit and total bilirubin > 1.5 × upper limit); (9) without disorder of renal function (Creatine or BUN/Urea > 1.5 × upper limit); without dialysis patients.

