## Outcomes

### Primary Outcomes

Validity endpoint is satisfaction rate of sedation, which equals to proportion of time in target sedation range (RASS score, 0 to −3) without use of rescue therapy of the total duration of study drug infusion. Safety endpoint is the incidence of hypotension (SBP < 90 mmHg), the incidence of hypoxia (SpO_2_ < 90%), and the incidence of bradycardia (HR < 75% baseline HR or HR < 50 bpm).

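### Hypotension is defined on SBP < 90 mmHg alone, so falls averted by blood-pressure support go uncounted; the listed monitor fields also omit SBP and SpO2

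*Protocol article*

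**What the plan says.** Primary Outcomes in the protocol article sets three safety events. The first is "Safety endpoint is the incidence of hypotension (SBP < 90 mmHg"; the other two are "the incidence of hypoxia (SpO_2_ < 90" per cent and "the incidence of bradycardia (HR < 75% baseline HR or HR < 50 bpm". None of them refers to treatment.

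Data Management names the captured monitor data as "monitors parameters: respiratory rate (RR), heart rate (HR), mean arterial pressure (MAP), body temperature, central venous pressure (CVP), perfusion index (PI), bispectral index (BIS", and the blood gas data as "Data of arterial blood gas analysis (ABG), including lactate level, pO2, GAP, ScvO_2". It also states that "all bedside instruments, including monitors, mechanical ventilators, and blood gas analyzers are connected into a central server", and it includes "usage and drip speed of vasoactive agent" among the medication data.

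Inclusion Criteria, within the ERAS definition, requires "systolic blood pressure >90 mmHg with no usage of vasoactive agent during screening stage". Recruitment places a screening evaluation before surgery. Allocation randomises after ICU entry, once researchers confirm that the patient is suitable, but does not say what that confirmation covers. No section addresses vasoactive drugs during study sedation.

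**The concern.** A blood pressure threshold measures haemodynamic depression cleanly only if support is absent or alike in both arms. If staff start or raise a vasopressor as pressure drifts down, the patient may never cross 90 mmHg and is recorded as event-free. The plan links the two at entry, where the SBP requirement is paired with absence of vasoactive drugs, but drops the link in the endpoint.

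The trial is open-label. Allocation blinds those who assess, record and analyse, yet also says that researchers are not blinded, and it does not list treating clinicians among the blinded. The decision to give support can therefore depend on the known sedative. Objectives states a hypothesis of non-inferior safety as well as availability, so a masked difference could be read as reassurance.

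The starting point is also unclear. The no-vasoactive requirement belongs to the screening stage, and surgery lies between the screening evaluation and randomisation. Hypotension or support already present on ICU arrival could then be mixed with effects of the study drug.

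**Working it through.** **Step 1. Endpoint variables against listed data.**

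| Primary safety event | Variable needed | Named in Data Management? |
|---|---|---|
| Hypotension | SBP | No (MAP is listed) |
| Hypoxia | SpO2 | No (pO2 from blood gases is listed) |
| Bradycardia | HR | Yes |

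One of three is named. SBP cannot be recovered from MAP alone, and pO2 from intermittent samples is not monitored SpO2.

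**Step 2. What the hypotension definition counts.**

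- SBP falls below 90, untreated: event.
- SBP falls below 90, then treated: event.
- SBP is held at or above 90 by support started or increased beforehand: no event.

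Only the third case is lost.

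**Step 3. Possible size.** The plan gives no expected rate for any safety event, so there is no figure of its own to reproduce here; its sample size rests on the sedation rate. All risks and averted shares below are assumptions. The formula is:

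observed incidence = underlying risk × (1 − share averted by support)

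*A difference shrinks.* Underlying risks 30% and 15%, half averted in each arm:
- 30% × 0.5 = 15%; 15% × 0.5 = 7.5%.
- The difference falls from 15 to 7.5 points. The risk ratio stays at 2.0.
- With 42 per arm, the excess falls from 0.15 × 42 = 6.3 to 0.075 × 42 = 3.15 patients.
- If only 10% are averted in each arm, the difference is 15 × 0.9 = 13.5 points.

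*A difference is hidden.* Same risks, half averted in the higher-risk arm only:
- 30% × 0.5 = 15%; 15% × 1 = 15%. The difference is zero.

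*A difference is created.* Equal underlying risk, 10% averted in one arm and 50% in the other:

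| Underlying risk, both arms | Observed, 10% averted | Observed, 50% averted | Spurious difference |
|---|---|---|---|
| 20% | 18% | 10% | 8 points |
| 30% | 27% | 15% | 12 points |
| 40% | 36% | 20% | 16 points |

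The direction depends on which arm receives more pre-emptive support, and the documents give no information on that.

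**Step 4. Baseline.** The vasoactive criterion applies at screening, the screening evaluation precedes surgery, and randomisation follows ICU entry. A suitability check exists at randomisation, but its content is not stated. Whether patients can be on support at randomisation cannot be settled from the text.

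**The case against.** **The threshold is objective.** SBP below 90 mmHg is measurable and applied identically in both arms, and leaving out treatment is not a contradiction. Putting vasopressor starts into the endpoint brings in a discretionary decision by unblinded staff, some of it for reasons unrelated to sedation. Counting every vasoactive agent would even score a vasodilator given for high pressure as hypotension. This stands. It rules out replacing the SBP-only endpoint, but not reporting a second version beside it.

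**The missing fields.** A reader might infer that two of the three safety endpoints cannot be derived. The documents do not support that. The article condenses a fuller protocol, all bedside monitors feed a central server, and Secondary Outcomes records vital signs during medication without naming them. The values are probably captured. What remains is a mismatch between two sections of the same article.

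**Treated hypotension.** A reader might infer that treating an episode removes it from the count. It does not, once SBP has fallen below 90.

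**The baseline.** A reader might infer that patients will be on vasoactive drugs at randomisation. The suitability check may exclude them; the article does not say.

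**The calculation.** Its inputs are assumed, and equal averted shares leave the risk ratio unchanged and the higher-risk arm still higher. That is correct. The figures show what could happen, not what is likely.

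**Conclusion.** The point holds in a limited form. The hypotension endpoint misses episodes that support keeps at or above 90 mmHg. Such support can differ between arms in an open-label trial, and the plan does not address it during sedation. The effect on the comparison may go either way, so a bias always towards no difference should not be claimed. Under the assumed inputs, a 15-point difference could be halved or vanish, and a spurious one of 8 to 16 points could appear. The real size is unknown because the documents give neither hypotension risks nor rates of pre-emptive support.

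This merits a change because the necessary drug data are already planned. The omission of SBP and SpO2 from the monitor list is a minor inconsistency.

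**What to change.** 1. In Primary Outcomes, keep the incidence of SBP < 90 mmHg as defined. Pre-specify beside it, by arm, the incidence of SBP < 90 mmHg or a new start or rate increase of a vasopressor or inotrope during study drug infusion, with vasodilators excluded.
2. Record SBP and vasoactive use, with agent and rate, at randomisation as baseline, so that hypotension or support already present is not counted as a drug effect. State whether the suitability check in Allocation repeats the screening-stage vasoactive criterion.
3. Reconcile Primary Outcomes with Data Management by naming SBP and SpO2 among the captured monitor fields.

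The cost is a few lines of wording, two fields from monitors already connected, and one extra analysis of drug data already collected, provided the records identify the agent. The drawback is that some starts or increases will have other causes and are decided by unblinded clinicians. That is why both versions should be reported: agreement would be reassuring, and disagreement would show how far the result depends on support. The change concerns measurement only and leaves patient management untouched.

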## Pharmacokinetic Sampling

A total of <20 mL of whole blood samples are collected in heparin tubes during the clinical trial. Opportunity blood sampling is used as sampling strategy, which is, 5, 15, and 30 min after initial dosing and 0, 10, and 30 min after changing pump speed. After direct centrifuging, a plasma aliquot is stored at −80°C until analysis. Remimazolam Besylate concentrations are measured using HPLC-MS/MS analysis.

## Statistical Methods

### General Statistics

A descriptive analysis of the data will be carried out. Qualitative variables will be represented by a frequency distribution of the percentages for each category, and quantitative variables will be explored using the Kolmogorov-Smirnov conformity test. The association between factors will be investigated using hypothesis contrast tests, with a comparison of proportions when both variables are qualitative (χ^2^, Fisher's exact test), a comparison of mean when one of them is quantitative (Student's *t*-test, analysis of variance (ANOVA), and the Mann-Whitney *U*-test or the Kruskall-Wallis test if they do not follow a normal distribution) and a bivariate correlation (Pearson correlation coefficient) when both are quantitative or the Spearman correlation if the conditions for application of the former are not met. For comparisons in related samples when one of them is quantitative, Student's *t*-test and/or ANOVA will be used (Wilcoxon or Friedman's test if they do not follow a normal distribution). The analysis will be completed using multivariate regression models. A survival analysis will be performed using the Kaplan-Meier method, and the log-rank test will be used for survival comparisons between groups. Effects will be considered to be significant with a *p* value of < 0.05.

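### A normality check on the trial's own data selects the test for the primary endpoint; neither resulting test is made against the 10% margin, and the rank-test branch has no scale on which to read it

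*Protocol article*

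**What the plan says.** Primary Outcomes defines the efficacy endpoint as the "proportion of time in target sedation range", "without use of rescue therapy of the total duration of study drug infusion". That is one number per patient, bounded between 0 and 100%.

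Sample Size Planning states the hypothesis as "non-inferiority satisfied rate of sedation on ERAS patients under mechanical ventilation in ICU" and adds that "the non-inferiority threshold is 10"%. It takes 82% for propofol and 92% for remimazolam, with α = 0.05 and 80% power.

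Statistical Methods, General Statistics, is the only place that says how groups are compared. There, "quantitative variables will be explored using the Kolmogorov-Smirnov conformity test". Two groups are then compared on a quantitative variable by Student's t-test or ANOVA, with the Mann-Whitney test or "the Kruskall-Wallis test if they do not follow a normal distribution". The decision rule is a p-value below 0.05. The section does not exempt the primary endpoint and does not mention the margin.

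**The concern.** The two branches answer different questions. The t-test concerns the difference in mean time in target, which is the scale of a 10-point margin. Mann-Whitney concerns whether a patient in one arm tends to rank above a patient in the other. It has no 10-point scale, and it gives little weight to how far a poor result falls short. If a normality check on the trial data picks the branch, the quantity estimated for the primary hypothesis is settled only after the data are seen.

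This matters because the two arms may well differ in shape. Values around 82% to 92% on a 0–100% scale tend to be left-skewed. Rescue therapy is described only for the experimental group, and time under rescue does not count as satisfactory. A subset of very low values confined to the remimazolam arm is therefore plausible. With such a subset, the rank test and the mean difference can point in opposite directions.

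**Working it through.** **1. The plan's own figure.** Inputs from Sample Size Planning: 82% and 92%, margin 10 points, 80% power. Read as a comparison of two binary proportions at one-sided α = 0.05:

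n per arm = (1.645 + 0.842)² × (0.82×0.18 + 0.92×0.08) / (0.92 − 0.82 + 0.10)² = 6.18 × 0.2212 / 0.04 = 34.2, rounded up to 35.

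With 15% loss: 35 / 0.85 = 41.2, rounded up to 42 per arm, 84 in total. The stated numbers reproduce. The calculation treats the endpoint as a yes/no rate and uses an absolute 10-point margin. Primary Outcomes makes the endpoint a time share per patient, so on that definition the rule for quantitative variables applies to it.

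**2. What each branch delivers.**
- Student's t at p < 0.05 tests a difference of zero, not of −10 points. It comes with a mean difference and standard error, so a limit to compare with −10 can be formed.
- Mann-Whitney at p < 0.05 tests whether one arm tends to rank higher. As written, nothing from it can be set beside 10 points.

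**3. How far the branches can diverge.** The documents give no SD, failure fraction or failure level, so every shape here is assumed. In each mixture the failing patients average 10% and remimazolam's true mean is 72%, against 82% for propofol. For the first row: 0.756×92 + 0.244×10 = 72.0. For the last row of the table: 0.861×82 + 0.139×10 = 72.0. Simulated at 42 per arm with beta shapes, 2,000 to 4,000 trials each:

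| Propofol SD | Remimazolam patients who do not fail | Failing | Mann-Whitney significantly favours remimazolam |
|---|---|---|---|
| 10 | mean 92%, SD 5 | 24.4% | 47–50% |
| 10 | mean 88.5%, SD 7 | 21% | 14–15% |
| 15 | mean 92%, SD 5 | 24.4% | 7–8% |
| 10 | same as propofol | 13.9% | 0.1–0.3% (favours propofol in about 20%) |

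The failing share in the second row follows from (88.5 − 72) / (88.5 − 10) = 0.21. In the first row the Kolmogorov-Smirnov test rejects normality in essentially every trial, so the Mann-Whitney branch is the one used. A one-sided 95% bound on the mean difference claims non-inferiority there in 7–8% of trials, slightly above the nominal 5% because of the skewness. At 35 per arm the 47–50% becomes about 43%.

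Under a plain shift (beta shapes with means 82% and 72% and equal concentration 5, 35 per arm), Mann-Whitney favours remimazolam in 0% of trials and propofol in 71%.

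**4. The gate itself.** Rejection rates at nominal 5%, n = 42, with mean and SD estimated from the sample:

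| Data | Uncorrected | Lilliefors |
|---|---|---|
| Normal | about 0% | about 5% |
| Beta, mean 82%, SD 15 | about 6% | about 69% |

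The protocol does not say which version is meant, so the same data can go to different branches depending on a software default.

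**The case against.** - **General Statistics may not govern the primary endpoint.** The section is generic, never names that endpoint, and the sample size is that of a binary rate. Analysed as a rate, the endpoint would go to χ² or Fisher and the normality check would be irrelevant. This stands as a real ambiguity. But the definition in Primary Outcomes is a time share, and no other comparison rule is given.
- **The t-test branch is not a margin test either.** This stands in full. Removing the normality check alone would not repair the plan; the margin comparison has to be written in as well.
- **A separate analysis plan may override this.** It may. The point concerns a rule that the protocol does state and that does not answer its own hypothesis, not a detail left out.
- **Stronger readings.** A reader might infer that the rule favours an inferior drug in half of trials. The documents do not support that. The figure needs about a quarter of patients failing and the rest clearly better than a tightly distributed control; other shapes with the same 10-point deficit bring it close to zero. A reader might also infer that the Kolmogorov-Smirnov test is badly miscalibrated. That holds only for the uncorrected version, and that version would send about 94% of the skewed samples to the t-test, not to the rank test. Nor would failures be hidden: the incidence of rescue in the experimental group is a listed secondary outcome. Finally, rank methods are not inherently unable to address a margin. A margin-shifted rank test or a Hodges-Lehmann interval could, although neither is stated and both target a location shift, not the mean difference.

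**Conclusion.** The point holds in this form: the stated rule lets the trial's own data choose what is estimated for the primary endpoint, and neither branch tests against the 10% margin. The t-test branch can be carried through to a margin comparison; the Mann-Whitney branch as written cannot.

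The chance that Mann-Whitney significantly favours remimazolam when its true mean is 10 points worse runs from about 0% to 50% at 42 per arm. That range reflects assumed distributions only. A reversal requires the two arms to differ in shape, and it did not occur under the plain shift. The choice of branch also depends on an unstated version of the normality test.

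The conclusion rests on reading the primary endpoint as quantitative, as Primary Outcomes defines it, and on taking Kolmogorov-Smirnov as the check behind the normality condition; it is the only one named. This should be fixed. The material does not support calling the trial's conclusion unsafe whatever the data look like.

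**What to change.** Remove the normality check for the primary endpoint and state one analysis in advance, whatever the shape of the data: the difference in mean per-patient time in target, remimazolam minus propofol, with a Welch or bootstrap confidence limit at the stated alpha. Non-inferiority is concluded if the lower limit lies above −10 points. State in the same place whether alpha is one-sided; the 35 per arm matches one-sided 0.05. Show any rank test only as a labelled sensitivity analysis.

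Align the rate used in Sample Size Planning with the time share in Primary Outcomes. If a yes/no responder endpoint is intended, define it and compare the confidence limit for the risk difference with the same margin. If the time share is intended, the sample size needs an assumed SD, which the protocol does not give.

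The analysis change costs a few sentences and needs no new data or patients. Moving the sample size to the time share would mean redoing that calculation, and the number could change.

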### Objectives

This study is designed to verify the hypothesis that compared with propofol, Remimazolam Besylate for Injection has non-inferiority availability and safety effect on sedation of ERAS patients under mechanical ventilation in ICU. The primary outcome is satisfaction rate of sedation and incidence rate of major clinical events. For availability evaluation, the secondary outcome includes incidence of delirium, time to weaning and extubation, difficulty of nursing, RASS, BIS and PI during medications. For safety evaluation, the secondary outcome includes 28-days survival, side-effect and vital signs during medications, total dose and dose per kilogram body weight of analgesic and sedatives and incidence of rescue therapy in experimental group.

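### The trial is designed and sized for non-inferiority with a 10% margin, but the stated analysis only tests for no difference at p < 0.05 and never uses the margin

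*Protocol article*

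**What the plan says.** The Objectives section of the protocol article says the study is "designed to verify the hypothesis that compared with propofol, Remimazolam Besylate for Injection has non-inferiority" availability and safety. Sample Size Planning restates this for sedation: "Remimazolam Besylate for Injection has non-inferiority satisfied rate of sedation on ERAS patients under mechanical ventilation in ICU". It gives "Setting inspection level: α = 0.05" without saying one- or two-sided, 80% power, and "the non-inferiority threshold is 10" percent. It assumes that "the target sedation rate of the propofol group is 82" percent and that the remimazolam rate is 92%. It arrives at 35 evaluable per arm, or 42 after 15% loss.

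The section on outcome analysis is General Statistics. It says: "The association between factors will be investigated using hypothesis contrast tests, with a comparison of proportions when both variables are qualitative", using χ² or Fisher's exact test. Quantitative outcomes get a t-test or ANOVA, or Mann-Whitney or Kruskal-Wallis if not normally distributed, with a Kolmogorov-Smirnov test used to examine the distribution. Survival gets a log-rank test, and multivariate regression is mentioned without detail. One decision rule closes the section: "Effects will be considered to be significant with a" p value below 0.05. No margin, shifted null, confidence interval or non-inferiority criterion appears there or elsewhere in the article.

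**The concern.** The null hypothesis behind the aim and the sample size is that remimazolam is worse by at least 10 points. The null behind the listed tests is that the arms do not differ. These are different questions. Failing to reject the second is no evidence against the first, especially at 35 to 42 patients per arm.

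Two things are at stake. Most of the power the trial was sized for is lost if success requires p < 0.05 on a difference test. The rule also leaves room for a non-significant difference to be reported as non-inferiority, which would be wrong most of the time when remimazolam is worse by exactly the margin.

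**Working it through.** **Inputs.** From Sample Size Planning: control rate 0.82, experimental rate 0.92, margin 0.10 (taken as absolute), α = 0.05, power 80%, 15% loss. From General Statistics: difference tests at p < 0.05, taken as two-sided. Endpoint treated as a binary rate, as in the sample-size section.

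**1. The plan's own figure.** n per arm = (z₁₋α + z₁₋β)² × [p_c(1−p_c) + p_t(1−p_t)] / (p_t − p_c + margin)².
- Variance sum: 0.82×0.18 + 0.92×0.08 = 0.1476 + 0.0736 = 0.2212. Denominator: (0.10 + 0.10)² = 0.04.
- One-sided 0.05: (1.645 + 0.842)² × 0.2212/0.04 = 34.2, so 35. With 15% loss, 35/0.85 = 41.2, so 42. Both match the article.
- One-sided 0.025: 43.4, so 44 (52 after loss). No match.
- A two-sided 0.05 difference test of 82% vs 92% needs about 177 per arm, and a one-sided one 139. No match.

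The size therefore belongs to a one-sided 0.05 non-inferiority test, not to the tests in General Statistics.

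**2. Remimazolam truly worse.** P(non-significant) = 1 − [Φ(d/SE − 1.96) + Φ(−d/SE − 1.96)], with SE = √{[0.82×0.18 + p_t(1−p_t)]/n}.
- d = 0.10 (72% vs 82%): SE = √(0.3492/35) = 0.0999 gives 83%; SE = √(0.3492/42) = 0.0912 gives 80%. Exact binomial enumeration of the χ² test gives 84% and 80%.
- d = 0.20 (62% vs 82%): 52% at 35 and 45% at 42.

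By exact enumeration at 72% vs 82%, a rule requiring the lower 90% limit to exceed −10 points declares non-inferiority about 6% of the time at either size.

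**3. Design assumptions true (92% vs 82%).**
- Two-sided difference test: 23.5% at 35 and 27.3% at 42 by normal approximation; 25% and 29% by exact enumeration.
- Confidence-limit rule, power = Φ(0.20/SE − z), with SE = √(0.2212/n) = 0.0795 at 35 and 0.0726 at 42:
  - 90% CI (z = 1.645): 81% and 87%.
  - 95% CI (z = 1.96): 71% and 79%.

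**4. Two possible results at 35 per arm, propofol 29/35.**
- Remimazolam 26/35: χ² p = 0.38, difference −8.6 points, 90% CI −24.6 to +7.5. Not significant, and non-inferiority not shown.
- Remimazolam 32/35: χ² p = 0.28, difference +8.6 points, 90% CI −4.5 to +21.6. Not significant, yet non-inferiority shown.

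The p-value rule treats these two results alike, although only the second meets the margin.

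**The case against.** The best defence is that General Statistics is a generic list of tests by variable type. It does not name the primary endpoint or say that non-significance means non-inferiority. This is a condensed article, its Dissemination section refers to a full protocol, and a primary test procedure may well sit there or in an analysis plan. Part of this stands: the misreading quantified above is a risk, not something the article prescribes. But the section is not silent. It fixes tests and one decision rule for all effects, and that rule does not test the stated hypothesis.

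Stronger readings that a reader might infer do not hold:
- That the listed tests can never establish non-inferiority. A significant result favouring remimazolam puts the lower 95% limit above zero, hence above −10 points.
- That a switch to Mann-Whitney makes a margin impossible. A shifted rank test or a Hodges-Lehmann limit can be compared with −10 points. The fault is that the article does not do this and lets the data choose the method.
- That every listed method excludes a margin. The unspecified regression could yield an interval, but none is stated or tied to the margin.
- That a non-significant result is likely however much worse remimazolam is. At a 20-point deficit the probability is 52% at 35 per arm and only 45% at 42. For a continuous analysis (SE = SD√(2/n)) it depends on an SD the article does not give: at 35 per arm and a 10-point deficit, about 1%, 45% and 71% for assumed SDs of 10, 20 and 30 points.

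**Conclusion.** The point holds. The hypothesis and sample size are for non-inferiority, while the stated decision rule tests no difference and ignores the margin. A non-significant result is uninformative about non-inferiority. The one route by which the stated rule would support the aim has about 25–29% probability under the design assumptions, against 81–87% for the 90% CI rule that the sample size implies.

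These figures assume an absolute margin and a binary endpoint. Primary Outcomes defines the endpoint as a proportion of infusion time, so if it is analysed as a mean per patient, the 82%/92% calculation does not give its power. The 81–87% also rests on remimazolam being 10 points better: at equal rates of 82%, exact enumeration gives the 90% CI rule about 31% at 35 per arm and 35% at 42. Whether an unseen document states a margin-based rule cannot be judged from the article.

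**What to change.** In General Statistics, for the sedation primary endpoint:
- Replace the p < 0.05 rule with the estimated difference (remimazolam minus propofol) and its confidence interval. Declare non-inferiority only if the lower limit is above −10 percentage points.
- State the sidedness of alpha. A two-sided 90% CI matches the stated sample size. A 95% CI requires restating power as about 71% at 35 evaluable per arm (79% at 42), or 44 evaluable (52 enrolled) per arm to keep 80%.
- Name the primary method in advance and do not let the Kolmogorov-Smirnov test choose it. If the analysis is of mean percent time in target, say that the present calculation does not give its power.

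For the primary safety endpoints (hypotension, hypoxia, bradycardia), report differences with confidence intervals. Do not claim non-inferior safety from non-significant tests, since no safety margin is stated. The difference tests can stay for secondary outcomes.

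The cost is a few sentences and no new data. With the 90% CI no patients are added; the 95% option costs either stated power or sample size.
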